### **5.3 Acute Rejection**

Despite the use of maintenance immunosuppression, acute cellular rejection is a common problem post lung transplant with 34% of adult LTx recipients experiencing at least one episode during the first year

post-transplant. The lung allograft is particularly susceptible to alloreactivity with the incidence of acute rejection being higher following LTx compared to other solid organ transplants. Whilst the direct effects of acute rejection are usually controlled and reversed following high-dose intravenous steroid treatment, the indirect effects remain problematic, with episodes of acute rejection being strongly associated with the later development of chronic lung allograft dysfunction (CLAD). Given the need for invasive transbronchial biopsies to provide a histological diagnosis of acute cellular rejection, we have previously evaluated biomarkers in the blood and BAL and their association with acute rejection (2-5). Functional assays of T cell and B cell function in the blood may identify patients at higher risk of acute cellular rejection. Analysis of the BAL is very useful in providing mechanistic insights into the immunology of graft function and rejection following LTx. However, BAL findings seen in acute rejection must be interpreted in the context of those described in stable lung transplant recipients, and after taking into account the confounding nature of chronic airway infection.

#### **5.4 Infection in immunosuppressed lung transplant recipients**

Infection is commonly encountered following LTx and is largely related to the use of immunosuppressive medication. We have a long-standing interest in how opportunistic infections such as CMV (8) and Aspergillus (9) have both direct effects on the lung allograft, as well as indirect effects through an association with CLAD. The airways, historically thought to be sterile, are now known to harbor a microbiota that changes in its constituents depending upon the health status of an individual. This lung microbiome consists of bacteria, viruses and fungi, which are in intimate contact with cells in the lung providing tonic stimuli to our immune system. As is routine clinical practice, the current study will also include a detailed prospective analysis of infections, and associated risk factors in the cohort of LTx recipients. In particular, we will determine the impact and interaction of bacteria, viruses and fungi in the transplanted lung, in order to inform improved treatment and prevention of CLAD.

## **28. STUDY PROPOSAL**

LTx saves lives, however the long-term viability of the allograft is limited by the immune response to it and the development of CLAD. The production of *de novo* anti-HLA alloreactive donor-specific antibodies (DSA) is deleterious to the graft and is associated with CLAD. However, the immune cell response following LTx and its relationship to the lung microbiome is poorly understood. We propose a thorough and integrated delineation of the immune response to LTx. We will obtain a comprehensive picture of the lower airway bacterial, viral and fungal communities in LTx recipients, and determine the implications of the lung microbiome on inflammation, lung tissue remodelling pathways and allograft function. Following LTx, we will have defined immune and physiological biomarkers of rejection that will better inform the use of appropriately focused immunosuppressive therapies with a

view to reducing CLAD and prolonging survival following LTx. Insights gained will extend beyond LTx to all types of solid organ transplantation.

## **29. RESEARCH PLAN**

### **Specific Aim #1: Defining HLA eplet mismatch scores**

**Rationale:** The humoral antibody-antigen immune response describes the interaction between anti-HLA DSA with the cognate non-self HLA molecule expressed within the lung allograft. HLA genes are highly polymorphic with over 10,000 HLA Class I and II alleles. Anti-HLA antibodies recognise specific exposed regions of the HLA antigen that consist of chains of amino acid sequence located within the complement determining regions, termed eplets.. Approximately 600 HLA Class I and II eplets have been described by Duquesnoy *et al.* (10) using the theoretical computer algorithm HLA-Matchmaker. Functional eplets specifically recognise HLA antibodies and are exposed within the binding groove demonstrating antigenicity, i.e. reactivity with antibody, and immunogenicity, i.e. ability to elicit immune response. LTx recipients are transplanted with HLA-mismatched donor lungs. HLA typing will be performed by Luminex sequence-specific oligonucleotide or sequenced-based typing for HLA-A, -B, -C, -DR and -DQ (Victorian Transplantation and Immunogenetics Service). The HLA-Matchmaker 500 pair (ABC and DRDQ eplet) program will be used as a research tool to assess eplet matching for all LTx (<http://www.hlamatchmaker.net/>). The calculated linear score of structural diversity for each LTx will be used for the subsequent studies looking at the impact of structural incompatibility on immune pathways and allograft dysfunction.

### **Specific Aim #2: Immune response in high eplet mismatch lung transplant recipients**

#### **vii) *De novo DSA production***

**Rationale:** Anti-HLA DSA may be present at the time of LTx (sensitised recipient) or develop *de novo* following LTx, and may be specific to HLA-class I and/or HLA Class II. The alloreactivity of DSA is determined by whether they are bound within the lung allograft, and whether they amplify an immune response. The C1q assay is a modification of the standard Luminex assay that distinguishes complement-fixing (and therefore injurious) from non-complement-fixing DSA. The clinical utility of the C1q assay has been demonstrated in renal transplantation, and similar studies are awaited in LTx. DSA can also be alloreactive via complement-independent pathways. NK cells and macrophages can be directly activated via the low-affinity Fc receptor resulting in antibody-independent cell-mediated cytotoxicity. Aim #2 will integrate DSA results with eplet mismatch scores and other immune markers to provide a comprehensive description of Antibody Mediated Rejection (AMR).

#### **viii) *B-cell specificity, phenotype and function***

**Rationale:** B cells can be alloreactive, either as precursors (naïve or memory B cells) of DSA-producing plasma cells or as antigen-presenting cells to allospecific T-cells. HLA tetramers provide an opportunity to track antigen-specific B cell responses longitudinally from the time of LTx. In LTx, the dynamics

and role of alloreactive B cells in producing anti-HLA DSA and graft dysfunction has not been described.

B cell subtypes will be phenotyped from the blood of LTx recipients by flow cytometry in the lab of [name] of immune cells will be assessed using a stimulated intracellular cytokine stain. The dynamics of B and T cell biology will be tracked longitudinally over the first 12 months, and will be correlated with eplet mismatch scores and *de novo* DSA production (assessed at 3 and 12 months post-transplant).

**ix) *Antibody-dependent NK cell cytotoxicity***

**Rationale:** The complement-independent mechanisms that lead to AMR are poorly understood, although recent work suggests that NK cells may be important effectors of Antibody-Dependent Cell-Mediated Cytotoxicity (ADCC). We have previously shown that NK cells are activated in LTx recipients and contribute to DSA-mediated allograft injury (5). Molecular signatures from allograft biopsies support the alloreactive potential of NK cells. We aim to use an *in vitro* NK-cell ADCC assay to analyse the role of DSAs in promoting NK cell activation. NK cells will be identified by flow cytometry (CD3-CD56+ lymphocytes) in the blood LTx patients at 3 and 12 months post-transplant.

**Specific Aim #3: Determine the immunological profiles of the lower airways of lung transplant recipients**

We will characterise the immunological environment of the lower airways of LTx recipients at each timepoint (i.e. 2 weeks, 3, 6, 9, 12 and 18 months) by RNAseq of immune cells isolated from the lavage fluid. We will perform Mass Spectrometry of the lavage fluid to characterise the metabolome, lipidome and proteome. Bioinformatic integration of these datasets (see Aim 5) will allow us to gain deep insight into the immunological profiles of the patient groups.

**Specific Aim #4: Identification of the bacterial, fungal and viral communities in lung transplant recipients**

*Bacterial and fungal community identification:* Fungal and bacterial DNA will be amplified and sequenced. The virome will be characterised, using two experimental approaches in order to ensure we capture a complete and informative dataset. First, PCR amplification will be used to analyse the total set of BAL samples informing on the carriage of a specific set of RNA and DNA viruses, including a panel of anelloviruses which we hypothesize will be highly relevant in the lung transplant setting. In a second step, we will refine the patient pool for analysis based upon the clinical, immunological, bacterial, fungal and viral PCR results and perform metagenomic sequencing providing us with in-depth unbiased data on viral carriage.

**Specific Aim #5: Bioinformatics and integration of microbial, immunological and clinical datasets**

Network-based approaches have emerged as a powerful way to study microbial systems and analyse high-dimensional datasets. Using the bacterial, fungal and viral sequencing datasets, we will construct and combine ecological networks using dissimilarity and correlation-based methods. This will firstly allow us to determine the extent to which bacterial, fungal and viral communities are connected by causal relationships, and in particular, we can identify “key-stone” species which would be predicted to play a major role in community dynamics and consequently the immunological and health status of the transplant recipient.

#### **Specific Aim #6: Applying microarray to describe the molecular phenotype of lung allografts**

The current standard of biopsy-based assessment of lung transplants is the ISHLT histology classification applied to transbronchial biopsies. This assessment is based largely on empirical classifications and expert opinions, and provides little insight into the pathophysiological and immunological drivers of CLAD. Microarray analysis establishes diagnostic patterns of abnormality (and normality), but as yet is not been rigorously applied in the LTx setting.

We will utilise Microarray Analysis at 3 and 12 months post-transplant, scores provided by the Molecular Microscope Diagnostic System used to guide diagnosis of T cell mediated rejection and AMR will be applied to the lung allograft biopsies provided. These Microarray results will be correlated with eplet mismatch scores and immune markers and CLAD.

#### **SUB-STUDY: Single Lung Transplant (SLTx) Recipients**

In this sub-study we will perform Specific Aims 3-5 of the main study, above, on the lavage fluid from both the transplanted lobe and the native lobe. The datasets generated from the different lobes will be compared in order to ascertain whether the immunological and microbiological characteristics of the transplanted lobe develops independently, or in parallel, with the native lobes. This analysis will inform whether the local microenvironmental changes within individual lobes influence the health trajectory of transplant recipients.

## **30. METHODOLOGY**

### **8.1 Patient Recruitment:**

All adult patients undergoing lung transplantation, and whose long-term follow-up will be at the Alfred Hospital will be invited to participate in the study. Patients would be enrolled prior to transplantation.

SLTx Sub-Study: Patients who are awaiting or receive a single lung transplant (SLTx) at the Alfred Hospital will be invited to take part in a sub study comparing their transplanted lung with their own

native (non-transplant) lung. These patients will be consented to the main study prior to transplant, and will be asked to sign an addendum of consent if they agree to take part in the sub study.

## **8.2 Sample Collection:**

**8.2.1** Blood and BAL research samples will be collected throughout the project at time points and quantities described here.

### **Pre-Transplant:**

At the time of transplant an additional 20mls of blood will be collected providing a research sample, this will be collected at the same time as the patients routine pre-operative bloods are being taken, not requiring additional intervention.

### **At Bronchoscopies:**

- e) As part of routine post-transplant management lung transplant recipients attend for surveillance bronchoscopy at 2 and 6 weeks and 3, 6, 9, 12 and 18 months post-transplant, at which point blood and BAL samples are collected.
- f) On occasions of clinical concern, additional bronchoscopies may be scheduled as part of patient care. At these clinical relevant bronchoscopies, blood and BAL samples are also collected.

At both the scheduled surveillance bronchoscopies and the clinically initiated bronchoscopies occurring within the project follow-up period an additional 20mls of blood and 30mls of BAL samples will be collected for this project at the same time as the routine clinical samples are collected.

**8.2.2** Transbronchial Biopsy Samples will be collected throughout the project at the time points described here:

At participant's routine 3 and 12month post-transplant bronchoscopy, two additional transbronchial biopsy bites will be collected and sent to Canada for Microarray Analysis.

**8.2.3** SLTx Sub-Study Sample Collection:

### **At Bronchoscopies:**

- a) As part of routine post-transplant management, all lung transplant recipients undergo a surveillance bronchoscopy day 1 post lung transplant. For participants who have consented

to take part in the SLTx Sub Study prior to transplant, 30mls of BAL sample will be collected during this bronchoscopy from both the recipient's non-transplant and transplanted lung.

- b) During Bronchoscopies as per 8.2.1, in addition to the sample collected as part of the project, participants who consent to take part in the SLTX Sub Study will have 30mls of BAL collected from their non-transplant lung.

### **8.3 Participant Involvement:**

All participants will be followed for a total of 3 years following lung transplant.

Lung transplant recipients enrolled in the study would not need to make any additional trips to the Alfred hospital nor undertake any additional investigations. Collection of research related samples at bronchoscopies will coincide with routine biopsy, blood and BAL collections and will not require additional procedures for the participants.

### **8.4 Sample Processing:**

At bronchoscopy, blood and BAL samples will be collected according to standard clinical protocols and forwarded to microbiology for routine diagnostic assessments. These microbiological results will be analysed as an outcome variable in the current study.

Remaining blood and BAL samples will be processed and centrifuged at the Alfred hospital to provide plasma and BAL supernatant samples for biomarker analysis. These samples will then be transported to our collaborators for analysis.

Transbronchial biopsy samples will be collected according to standard clinical protocols; the tissue will be placed into RNAlater and shipped by courier to Alberta, Canada at ambient temperature to Alberta Transplant Applied Genomic Centre (ATAGC) for analysis.

## **31. INCLUSION/EXCLUSION CRITERIA**

Approximately 150 patients will be enrolled at The Alfred Hospital

### **Inclusion Criteria**

- Adults  $\geq 18$  years of age
- Lung Transplant Recipients
- Provide Written Consent

## Exclusion Criteria

- Long Term Follow-Up not planned for The Alfred Hospital

## 32. ANALYSIS:

Descriptive statistics will be used to determine the baseline and clinical characteristics of the subjects in the study. Univariate analysis of the biomarkers and their association with the clinical end-points of acute rejection and CLAD will be performed using the Chi-square test for equal proportion, Student's t test for normally distributed continuous variables and the Mann-Whitney U test for non-normally distributed variables. Time to acute rejection and CLAD will be analyzed using univariate and multivariate Cox proportional hazards regression, adjusting for potential confounding factors and reported using the Kaplan Meier curves. All analysis will be performed using SAS version 9.2 (SAS Institute Inc., Cary, NC, USA). A two-sided p-value of 0.05 will be considered to be statistically significant.

### **34. ABBREVIATIONS**

|      |                                               |
|------|-----------------------------------------------|
| ADCC | Antibody-Dependent Cell-Mediated Cytotoxicity |
| AFOP | Acute Fibrinoid Organizing Pneumonia          |
| AMR  | Antibody Mediated Rejection                   |
| BAL  | Broncholaveolar Lavage                        |
| BOS  | Bronchiolitis Obliterans Syndrome             |
| CLAD | Chronic Lung Allograft Dysfunction            |
| DAD  | Diffuse Alveolar Damage                       |
| DSA  | Donor Specific Antibodies                     |
| HLA  | Human Leukocyte Antigens                      |
| LTx  | Lung Transplant                               |
| MFI  | Mean Fluorescence Intensity                   |
| MHC  | Major Histocompatibility Complex              |
| NK   | Natural Killer                                |
| OB   | Obliterative Bronchiolitis                    |
| PCRs | Polymerase Chain Reactions                    |
| RAS  | Restrictive Allograft Syndrome                |
| Tfh  | Follicular Helper T Cells                     |

## **35. SUMMARY**

Transplantation saves the lives of patients with end stage lung disease. Better operative techniques, anaesthesia, organ preservation and more potent immunosuppression have improved outcomes significantly but long-term graft survival remains unchanged. Transplanted lungs are lost due to an ill-defined process called chronic lung allograft dysfunction (CLAD) that is characterized by either fibrosis of the airways (bronchiolitis obliterans syndrome = BOS) or of the lung architecture (restrictive allograft syndrome = RAS) (1). CLAD is characterised by a drop in lung function, that once established is irreversible. The major risk factors for CLAD are i) acute rejection as diagnosed on lung biopsy and ii) infection, particularly CMV and aspergillus. To date, biomarkers have not been identified that can diagnose acute rejection or predict the early onset of CLAD.

We have previously explored a number of biomarkers and demonstrated an association with allograft dysfunction following lung transplant (LTx). We have shown that activin and follistatin levels vary with time from LTx and reflect a proinflammatory environment (2,3). We continue to explore the role of NK cells following LTx having previously shown that NK cells become activated in patients undergoing acute rejection or CMV infection (4, 5). Collaborative research with the Doherty Institute has demonstrated a link between immune cells that control CMV and the later development of CLAD (6). We now wish to extend this biomarker approach with a new prospective cohort of LTx patients who will provide blood and BAL samples to allow further interrogation of immune and infectious links to allograft dysfunction following LTx.

Identifying CLAD at an early stage, may allow therapeutic interventions to interrupt the progression to irreversible damage to the transplanted lung. We propose to analyse in both a cross-sectional and longitudinal study whether a series of biomarkers can predict for episodes of acute rejection or the development of CLAD in a cohort of patients undergoing LTx at the Alfred Hospital.

## **36. HYPOTHESIS**

The identification of biomarkers of immune function and infection in the blood and lung will predict episodes of acute rejection and the onset of chronic lung allograft dysfunction (CLAD) following LTx.

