## **37. BROAD PROJECT AIMS**

4.1. To establish the immune response in the serum and bronchoalveolar lavage (BAL) as measured cross-sectionally and longitudinally during the three year post-LTx and the association with later episodes of acute rejection or the subsequent development of CLAD.

4.2. To determine whether episodes of viral, fungal or bacterial infection in the LTx recipient trigger further increases in the secretion of these biomarkers and thus act as an inflammatory stimulus.

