**Specific Aim #3: Determine the immunological profiles of the lower airways of lung transplant recipients**

We will characterise the immunological environment of the lower airways of LTx recipients at each timepoint (i.e. 2 weeks, 3, 6, 9, 12 and 18 months) by RNAseq of immune cells isolated from the lavage fluid. We will perform Mass Spectrometry of the lavage fluid to characterise the metabolome, lipidome and proteome. Bioinformatic integration of these datasets (see Aim 5) will allow us to gain deep insight into the immunological profiles of the patient groups.

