### 43. ANALYSIS:

Descriptive statistics will be used to determine the baseline and clinical characteristics of the subjects in the study. Univariate analysis of the biomarkers and their association with the clinical end-points of acute rejection and CLAD will be performed using the Chi-square test for equal proportion, Student's t test for normally distributed continuous variables and the Mann-Whitney U test for non-normally distributed variables. Time to acute rejection and CLAD will be analyzed using univariate and multivariate Cox proportional hazards regression, adjusting for potential confounding factors and reported using the Kaplan Meier curves. All analysis will be performed using SAS version 9.2 (SAS Institute Inc., Cary, NC, USA). A two-sided p-value of 0.05 will be considered to be statistically significant.

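### The hypothesis is about predicting rejection and CLAD, but the analysis plan tests only association at p = 0.05 and has nothing that measures prediction

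*Supplement*

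**What the plan says.** The passages below are from protocol version 4.0 (16 February 2021), the latest in the supplement. No separate analysis plan is shown.

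- **Section 36, Hypothesis:** biomarkers of immune function and infection "will predict episodes of acute rejection and the onset of chronic lung allograft dysfunction (CLAD) following LTx".
- **Section 35, Summary:** the study will examine "whether a series of biomarkers can predict for episodes of acute rejection or the development of CLAD".
- **Section 37, Aim 4.1:** the wording here is weaker. The immune response is to be described together with "the association with later episodes of acute rejection or the subsequent development of CLAD".
- **Section 43, Analysis:** it plans "Univariate analysis of the biomarkers and their association with the clinical end-points of acute rejection and CLAD" by chi-square, t and Mann-Whitney tests, then "univariate and multivariate Cox proportional hazards regression, adjusting for potential confounding factors", with Kaplan-Meier curves. The only decision rule is "A two-sided p-value of 0.05 will be considered to be statistically significant".
- **Section 40, Specific Aim 3:** candidate markers will be measured "by RNAseq of immune cells isolated from the lavage fluid" and by "Mass Spectrometry of the lavage fluid to characterise the metabolome, lipidome and proteome". Specific Aim 4 adds bacterial, fungal and viral communities. The number of candidate markers is not stated.

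**The concern.** A hazard ratio or a group difference shows that a marker is related to the outcome. It does not show how well the marker separates patients who will reject from those who will not, whether predicted risks are accurate, or how much it improves on the risk factors that Section 35 itself names (earlier acute rejection, CMV, aspergillus). A marker can be clearly significant and still be of little use for prediction.

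Selection makes this worse. When markers are picked from many candidates and judged in the same patients, the picked ones look better than they are. Section 43 plans no resampling, hold-out set or external cohort that would show this. The study could then present markers as predictive without evidence that they predict, although Section 39 wants them to inform immunosuppressive treatment.

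**Working it through.** The documents give no power, effect size or event target, so there is no figure of the plan's own to reproduce. The check has two parts.

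**Inputs**
- Sample size: about 150 (Section 42).
- First-year acute rejection: 34% (Section 38, subsection 5.3). This is a background rate, assumed here to apply to all 150 patients.
- Threshold: two-sided 0.05, no adjustment (Section 43).
- Number of candidate markers m: not given. Assumed range 10 to 20,000.

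Events: 0.34 × 150 = 51, leaving 99 patients without rejection.

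**1. How well does a just-significant marker separate patients?**
- Mann-Whitney: the null standard error of the AUC is √[(51 + 99 + 1) / (12 × 51 × 99)] = √(151 / 60,588) = 0.0499. The AUC at p = 0.05 is 0.5 + 1.96 × 0.0499 = **0.598**.
- t test: the standardised difference at p = 0.05 is 1.96 × √(1/51 + 1/99) = 0.338. The AUC is Φ(0.338 / √2) = **0.594**.
- Cox model, per SD of the marker: HR = exp(1.96 / √51) = **1.32**.
- Even p = 0.001 corresponds to an AUC of only 0.664 (Mann-Whitney).

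**2. How good can pure noise look after selection?**

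Independent noise markers were simulated for 51 patients with and 99 without rejection, and the largest apparent AUC among m markers was averaged over simulated data sets. The true AUC is 0.50 throughout. The chance of at least one p < 0.05 for one endpoint is 1 − 0.95^m.

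| Candidates m (assumed) | Chance of at least one p < 0.05 | Mean apparent AUC of the best |
|---|---|---|
| 10 | 40% | 0.59 |
| 20 | 64% | 0.61 |
| 100 | 99.4% | 0.64 |
| 1,000 | about 100% | 0.67 |
| 20,000 | about 100% | 0.70 to 0.71 |

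A score that sums the five best noise markers looks better still, with a mean apparent AUC of 0.63 (m = 10), 0.73 (m = 100) and 0.80 (m = 1,000).

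The last two rows of the table apply only if omics features are screened one at a time. Correlation between markers lowers the chance of at least one false positive, but not the expected number, 0.05 × m per endpoint.

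**The case against.** There is a fair case on the other side, and parts of it stand.

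- **The plan promises association, and that is what it delivers.** Aim 4.1 and Section 43 agree with each other; only the hypothesis and summary say predict. A reader might infer that the study will report noise markers as predictors. The documents do not support that, because reporting under Section 43 would be of associations. It is what could happen if results are written up in the language of the hypothesis.
- **Adjusted Cox regression partly tests added information.** This stands. If the adjustment set holds the known clinical risk factors, a significant adjusted marker carries something beyond them. But the covariates are not named, and the test does not say how much prediction improves.
- **The large candidate counts are not in the plan.** This also stands. Specific Aim 3 sends the RNAseq and mass-spectrometry data to integration under Specific Aim 5, which describes network methods. The plan does not say that each feature will also be tested singly, nor that a best marker will be picked by AUC. The simulation shows what selection can do; it does not forecast this study's results.
- **A separate plan could add the missing measures.** One might read Section 43 as committing every analysis to the listed methods, but its sentence about all analysis fixes the software (SAS 9.2), not the methods. Resampling details could be left to a later document. The conflict between a predictive hypothesis and a p-value criterion is nevertheless inside the protocol.

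**Conclusion.** The point holds as a mismatch between question and method. Sections 35 and 36 ask about prediction, while Aim 4.1 and Section 43 supply association tests and hazard ratios at an unadjusted 0.05. Followed as written, the plan cannot show predictive performance.

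That conclusion does not depend on the number of markers. Its size is that the plan's only criterion is met by a marker with an AUC of about 0.59 to 0.60, which barely separates patients. This assumes 51 events, and fewer events would change the figure.

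The risk of noise being taken for prediction is real but conditional. It is substantial at 10 to 20 independent candidates and near certain at 100. It reaches apparent AUCs of 0.67 or more only if about 1,000 or more features are screened singly. The documents give no CLAD rate, so none of this can be sized for CLAD. The plan should be changed before any marker is reported as predictive.

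**What to change.** Add to Section 43, for any claim of prediction:

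1. Use only samples taken before the event.
2. Report the C-index or time-dependent AUC, and calibration.
3. Report the gain over a model with clinical risk factors alone, and name those factors.
4. Correct all of these for optimism by bootstrap or repeated cross-validation. Repeat marker selection inside each resample, and resample patients rather than samples, since each patient contributes several.

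The minimum alternative is to describe a marker that meets only the p-value as associated, and to reword the hypothesis and summary to match Aim 4.1.

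**Cost:** text and computing time, with no new patients or samples. Reported performance will look less favourable. Restricting to pre-event samples leaves fewer usable events at the later sampling times, which run to 18 months. Whether the approach is feasible for CLAD cannot be judged until the sponsor states an expected CLAD rate.
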